### Sample size

There is so far still no definite sample size calculation for fMRI research; however, as a result of previous fMRI studies, there should be at least 10 participants in each group to obtain brain imaging with statistical significance [18]. Combining the preceding clinical trial experiences all over the world recently with the withdrawal rate, we plan to enroll a total of 40 participants with 20 patients in each group.

### Ethics

This clinical trial will be carried out in accordance with the Declaration of Helsinki, as well as reviewed and approved by the Medical Ethics Committee Board of Sichuan Integrative Medicine Hospital, Chengdu, Sichuan, China (number: 2016KY-01). All of the participants will be requested to sign the written informed consent form before randomization. The present study is financially supported by the National Natural Science Foundation of China (number: 81503670), and the clinical trial was registered in Chinese Clinical Trials Registry with the identifier number ChCTR-IPC-16007832.

### Procedure

All of the potential participants will be initially assessed according to the inclusion and exclusion criteria by the physicians. After completing a screening test, the eligible participants will be asked to sign the written informed consent before randomization. The study subjects will then enter a baseline period for 1 week without any treatment. Subsequently, they will receive the intervention in the light of their group allocation for 4 weeks. All of the patients will be required to provide blood specimens for testing relevant indexes, as well as to be evaluated by study-related scales, MSMSMS, and fMRI scan before and after treatment. Two weeks after the end of treatment, patients in both groups will be followed up to assess the curative effect and safety again (Fig. 1).

**Fig. 1 Fig1:**
[figure not shown]
Study flowchart

### Randomization

The eligible participants will be assigned randomly to two groups in a ratio of 1:1. The random number table will be performed by the investigator who has no direct contact with the participants or the assessors to have access to the treatment procedures and outcomes. The randomization number will be sealed in a predetermined randomization opaque envelope. The patients’ screening sequence numbers will be printed on the outside of the envelope, whereas the group names will be printed inside. The envelope containing an allocation sequence number for each patient will be opened right after each patient is verified to meet the eligibility criteria and has signed the written informed consent form. If any error or disclosure regarding randomization occurs, a new randomization sequence will be generated starting from the problematic serial number and applied to subsequent patients.

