### Primary outcome

#### Pittsburgh Sleep Quality Index

The Pittsburgh Sleep Quality Index (PSQI), a self-rated questionnaire that evaluates sleep quality and disturbance over 1 month [20], is applied as the primary outcome measurement for clinical effectiveness assessment. The constructive validity and reliability of the PSQI to measure changes of sleep quality have been confirmed in previous studies all over the world. It is widely used to measure response to treatment in research studies and clinical trials. The PSQI is comprised of 19 items which consist of the following seven component scores: subjective sleep quality, sleep latency, sleep duration, sleep efficiency, sleep disturbance, use of hypnotic medication, and daytime dysfunction. Each item is weighted equally on a 4-point scale, from 0 to 3, with 0 indicating no dysfunction and 3 indicating the worst dysfunction. The seven component scores are then added to provide a global PSQI score. In general, a lower global score reflects a better sleep quality [21].

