### Secondary outcome

#### Micro-movement sensitive mattress-type sleep monitoring system

All of the study subjects will be measured for two nights (baseline: after randomization and before treatment, after the completion of treatment) in a sleep laboratory with a sound-attenuated, light-controlled, and temperature-controlled room. The TDM-6000 micro-movement sensitive mattress-type sleep monitoring system (MSMSMS) will be conducted to precisely obtain the continuous dynamic physiological parameters of the patients at night, as well as to compare the proportion of deep sleep, light sleep, and rapid eye movement (REM) sleep during the sleep period. During assessment, patients will be permitted to sleep optionally based on their habitual sleep time, with the recording time ranging from the moment of patient lying on the bed to the time of getting up. Sequentially, we can analyze the sleep architecture/structure, and accurately identify the various kinds of sleep disorders.

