#### Hamilton Depression Scale and Hamilton Anxiety Scale

Changes in levels of mood disorder will be measured on the Hamilton Depression Scale (HAMD) and the Hamilton Anxiety Scale (HAMA).

There are three types of HAMD scale, each with 17, 21, or 24 items. The 24-item HAMD scale will be used to evaluate the depressive condition in this trial. According to the score standard, a normal score is <8; a score ≥8 and <20 indicates that the patient has mild depression; a score ≥20 and ≤35 indicates that the patient has moderate depression; and a score >35 indicates that the patient has severe depression. Typically, the higher score reflects the more severe depression [22].

To assess anxiety, there is a 14-item self-rating questionnaire for evaluating the anxiety condition of last week. Based on the score standard, answers are scored on a 0–4 scale, with 0 indicating no symptoms and 4 indicating the worst anxiety condition, with a range in total score from 0 to 56.

In general, the normal threshold is 6 points; scores ranging from 0 to 5, from 6 to 13, from 14 to 20, from 21 to 28, and as 29+ are typically used to rate anxiety as none, mild, moderate, severe, and extremely severe, respectively. In general, the higher the score, the more severe the anxiety is.

In this study, both HAMD and HAMA will be evaluated twice (before and after treatment).

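### Allocation is revealed before the untreated baseline week, so the sleep-lab baseline, and possibly the baseline PSQI, follow it, and losses in that week are post-randomisation

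*Protocol article*

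**What the plan says.** Four places in the protocol article set the order of events.

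- **Procedure, consent:** after screening, "the eligible participants will be asked to sign the written informed consent before randomization".
- **Randomization:** the envelope "will be opened right after each patient is verified to meet the eligibility criteria and has signed the written informed consent form".
- **Procedure, run-in and treatment:** "The study subjects will then enter a baseline period for 1 week without any treatment". Then: "Subsequently, they will receive the intervention in the light of their group allocation for 4 weeks".
- **MSMSMS section:** the two sleep-lab nights are dated "baseline: after randomization and before treatment, after the completion of treatment".

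For the other measures, Procedure says only that patients are "evaluated by study-related scales, MSMSMS, and fMRI scan before and after treatment". The primary outcome, the PSQI, is "a self-rated questionnaire that evaluates sleep quality and disturbance over 1 month". The Blinding section accepts that patients cannot be blinded, and the Discussion lists this as a limitation. Neither place mentions the baseline measurements or the untreated week.

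**The concern.** A baseline value should be one that the allocation could not have influenced. Here the arm is assigned about a week before treatment starts, to patients who are not blinded, and the primary measure is the patient's own rating. Satisfaction or disappointment with the assigned arm could colour whatever is rated in that week. The analysis uses baseline values: the Statistical analysis section plans ANCOVA to adjust for baseline characteristics, the Hamilton section speaks of changes in mood, and the fMRI data processing section relates changes in imaging measures to clinical outcomes.

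The second consequence is attrition. An untreated week between allocation and treatment gives a patient who dislikes her arm time to leave, and withdrawal at the participant's own request is allowed. Such a patient has already been randomised and belongs to the intention-to-treat population, possibly with no treatment and no post-treatment score.

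**Working it through.** The plan gives no figure to reproduce on this point. The check is one of sequence, followed by simple algebra for the size.

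**1. Is the order really allocation, then baseline week?** Procedure alone does not say when randomisation happens; it says only that consent precedes it. It does put both eligibility assessment and consent before the baseline week. The Randomization section opens the envelope immediately once those two conditions are met. Together they give: eligibility, consent, envelope, one untreated week, four weeks of treatment. The MSMSMS section agrees independently, since its baseline night falls after randomisation. That wording does not look like a slip: the article writes of events before randomisation where it means them, for consent (Procedure) and for the laboratory and ECG tests (Safety monitoring).

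**2. Which baseline measures are exposed?**

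- MSMSMS: post-randomisation as stated. It is a device recording, so less open to reporting bias than a questionnaire.
- PSQI: dated only as before treatment. Procedure groups the scales with MSMSMS and fMRI, and the text leaves no interval between consent and envelope in which to take it. A PSQI at screening is not ruled out.
- HAMD and HAMA: each has a threshold in the inclusion criteria, so each must be scored before the envelope is opened. The text does not say whether that score also serves as baseline.
- MRI and blood: dated only as before treatment.

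**3. What would a shifted baseline do?** Let δ be the true between-arm difference in mean post-treatment score, with true baseline means equal. Let knowledge of the arm add b points to the baseline of one arm only, and let β be the within-arm regression slope of post-treatment on baseline score.

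- Post-treatment scores alone: contrast = δ, so the bias is 0.
- Change from baseline: contrast = δ − b, so the bias is b in size.
- ANCOVA: contrast = δ − βb, so the bias is βb in size.

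The documents give neither b nor β. Assuming β between 0.3 and 0.7, each point of shift moves the ANCOVA contrast by 0.3 × 1 = 0.3 to 0.7 × 1 = 0.7 points, and the change contrast by 1 point. The effect is proportional to b. An arm whose baseline is pushed up looks more improved than it is.

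**4. What does a loss in the week cost?** The Sample size section plans 20 patients per arm, so each loss is 1/20 = 5% of an arm. The documents give no loss rate for this week. If 2.5% to 10% of all randomised patients left in it (an assumed range), that would be 0.025 × 40 = 1 to 0.10 × 40 = 4 patients.

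**The case against.** The strongest reply is that the text does not show the primary outcome to be affected. A reader might infer that the baseline PSQI is certainly completed by patients who know their arm. The documents do not support that: no section dates the PSQI relative to randomisation, and none says when the patient is told her group. The study flowchart and trial processes chart could not be read here and may settle both. For HAMD and HAMA the text leans the other way. They are scored for eligibility and are said to be evaluated only twice, so the screening score may be the baseline. The same could hold for the PSQI. The PSQI also looks back over a month, so even when completed at the end of the baseline week, most of the time it covers precedes allocation. All of this stands, and it makes the PSQI part conditional.

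It is also true that the between-group test named first is one-way ANOVA, with ANCOVA secondary, and that no change-score analysis is specified for the PSQI. If the ANOVA is run on post-treatment scores, the baseline route does not touch it.

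On losses, a reader might infer that intention-to-treat is invalidated. It is not: the plan keeps that principle, provides for multiple imputation if needed, and says that withdrawals were considered in setting the sample size. What remains is that these losses are avoidable and could differ by arm.

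Two further inferences should be set aside. Recruitment draws partly on an acupuncture department, but no proportions are given, so nothing can be said about how many patients would prefer acupuncture. And the HAMA is introduced with the words "there is a 14-item self-rating questionnaire for evaluating the anxiety condition of last week", which raises a question about who rates it. That question is separate and does not depend on when the envelope is opened.

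**Conclusion.** The point holds in a limited form, with moderate severity. The text itself establishes that allocation comes before the whole untreated week, that the sleep-lab baseline is post-randomisation, and that any loss in that week is post-randomisation at 5% of an arm per patient.

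Influence on the baseline PSQI is a risk and not a demonstrated fault. It rests on two assumptions: that the PSQI is completed in that week, and that patients learn their arm when the envelope is opened. The second is the natural reading where patients are unblinded and no rule withholds the allocation. If both hold, change-score and ANCOVA contrasts are biased in proportion to a shift of unknown size and direction; a comparison of post-treatment scores alone is not. The Discussion's admission that patients are unblinded covers neither consequence.

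**What to change.** For patients still to be recruited:

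- Open the envelope only at the end of the baseline week, after the baseline PSQI, HAMD, HAMA, MSMSMS, blood and MRI assessments are complete and eligibility has been re-confirmed.
- Amend the Randomization section accordingly, and re-date the MSMSMS baseline to before randomisation.
- State in Procedure when the baseline PSQI is completed relative to the opening of the envelope.

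No extra visit or staff is needed. The cost is that some sleep-lab, blood and MRI assessments will be spent on patients who leave before randomisation. The trial is already recruiting, so patients enrolled so far will have followed the existing order and the trial will contain both procedures. The report should say which patients followed which order, and give by arm any losses between envelope opening and first treatment.

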### Blinding

Considering the significant difference of treatment and the specificity of acupuncture, double blinding of the clinician and patient is unfeasible. However, to guarantee the integrity of this trial, we will strictly conduct randomization allocation and appoint different people to perform therapy, assessment, and statistical analysis according to the principle of blinding.

### Interventions and comparison

#### Rationale for acupuncture (selection of acupoints)

Based on the theory of acupuncture and TCM, perimenopausal insomnia is closely related to the liver. First, the liver plays a vital role in the sleep rhythm and the pathogenesis of sleep problems. Second, emotional disorder, as one of the major factors of insomnia, is also influenced significantly by the liver. According to the basic theory of TCM, the liver governs regulating emotion. Hence, we determined the intervention formula from the liver, and selected the following acupoints as the primary acupuncture points: Baihui (DU20), Sishencong (EX-HN-1), Anmian (EX-HN-54), Ganshu (GB18), Geshu (GB17), Taichong (LI3). Moreover, on the basis of TCM differentiation, subsidiary acupoints are: Taixi (KI3), Quchi (LI11), and Sanyinjiao (SP6) for hyperactivity of liver yang; Xuehai (SP10) and Hegu (LI14) for stagnation of liver qi and blood; Weishu (GB21), Zusanli (ST36), and Liangqiu (ST34) for stagnation of liver qi invading the stomach; Xinshu (GB15), Neiguan (PC6), and Shenmen (HT7) for stagnation of liver qi invading the heart; and Shenshu (GB23) and Taixi (KI3) for liver hyperactivity and kidney deficiency (Table 1).

**Table 1 Tab1:** Acupuncture points

Syndrome differentiation	Primary point	Additional point
	Baihui (DU20), Sishencong (EX-HN-1)	
	Anmian (EX-HN-54), Ganshu (GB18)	
	Geshu (GB17), Taichong (LI3)	
Hyperactivity of liver yang		Taixi (KI3), Quchi (LI11), Sanyinjiao (SP6)
Stagnation of liver qi and blood		Xuehai (SP10), Hegu (LI14)
Stagnation of liver qi invading the stomach		Weishu (GB21), Zusanli (ST36), Liangqiu (ST34)
Stagnation of liver qi invading the heart		Xinshu (GB15), Neiguan (PC6), Shenmen (HT7)
Liver hyperactivity and kidney deficiency		Shenshu (GB23), Taixi (KI3)

#### Intervention group

The acupuncture points are identified in accordance with the method of point location issued by the World Health Organization (WHO) [19]. After disinfecting the skin on the point local areas, all of the acupoints are punctured by sterile, disposable filiform needles produced by Suzhou Hwato Medical Instruments Co. Ltd (Suzhou, China). The needles are 40 mm in length and 0.25 mm in diameter. The depth of insertion is adjusted based on the standard permissible depth of insertion for each acupoint. Baihui (DU20) will be punctured obliquely with the needle tip towards Qianding (DU21), and Sishencong (EX-HN-1) will be inserted aslant with all the pinpoints towards Baihui (DU20). Needle manipulation will be applied to achieve De Qi sensation, which is manifested as a numb, distended, and aching sensation. The needles will be maintained for 30 minutes in each session, and then removed with clean cotton balls to avoid bleeding. During the treatment period, the needles will be manipulated twice every 10 minutes with intermittent stimulation and each manual performance will last for 10 seconds. Every patient will be treated with acupuncture once per day for 6 consecutive days per week with a 1-day interval and will receive 24 sessions of acupuncture in total during a period of 4 weeks.

#### Control group

The participants in the control group will be prescribed oral administration of estazolam tablets (1 mg 30 minutes before sleep once per day for 4 weeks; 2 mg for severe insomnia) which are commonly used for insomnia. The estazolam tablets are produced by Forth Medicine Pharmacy CO.., Ltd (Changzhou, China) (Approval No.: H32020450).

#### fMRI examination procedure

The MRI examination (Signa 3.0 T Magnetic Resonance Imaging Scan; GE General Electric Company) will be performed to collect brain images offering more visualized proof. The MRI protocol for this study consists of the following parameters: high-resolution three-dimensional T1 weighting brain volume (Bravo) sequence scanning: repetition time (TR) of 8.16 ms, echo time (TE) of 3.18 ms, flip angle 7°, 256 × 256 mm^2^ field of view (FOV), voxel size of 1 × 1 × 1 mm^3^, 180 sections of 1.0-mm thickness. Before scanning, the subjects will be requested to keep quiet and their eyes closed, especially not to think something and to avoid sleep. In order to ensure the participants stay awake, the researcher will inquire of the subject whether they are awake during and after the scanning procedure. Both of the intervention groups will be examined twice (before and after treatment).

#### fMRI data processing

Functional MRI data will be processed by statistical parametric mapping (SPM8) of MATLAB2009b, DPARSF, and Freesurfer (http://surfer.nmr.mgh.harvard.edu/) software packages. Original data will be corrected; physiological artifacts, slice timing, affine head motion, and nonbrain extraction will also be implemented. Moreover, spatial smoothing and temporal filtering will be applied. Cortical surface reconstruction will be performed to improve structural–functional coregistration using FreeSurfer’s register tool (http://surfer.nmr.mgh.harvard.edu/), and then the cortex thickness will be calculated. The cortex thickness, superficial area, and volumetric of every group will be compared using a paired *t* test (*p* < 0.001, cluster size > 100 vertices). The cortex thickness, the local consistency changes of the brain region, and clinical outcomes with significant statistical differences will be analyzed by multiple regression analysis. Then we will acquire the brain regions correlated with an acupuncture clinical effect via analyzing the correlation index values *R* and *P* with the change of cortex thickness, ReHo of brain region, and clinical outcomes.

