As a chief component of Traditional Chinese Medicine (TCM), acupuncture has been used frequently in the treatment of a wide range of health problems, especially including sleep disturbance and mood disorder, in China and throughout the world [11, 12]. Previous studies certified that acupuncture appears to have an irreplaceable effect in treating insomnia and is able to significantly improve anxiety and depression [13]. Our pilot study also suggested that acupuncture treatment is effective in increasing sleep quality and improving emotional condition [14]. Consequently, it was believed that acupuncture may have great effect on sleep disorders and mood disturbances. Although there are some available studies demonstrating the benefits of acupuncture treating insomnia via evaluation using clinical effectiveness scales, it is still difficult to list more intuitive evidence, such as functional magnetic resonance imaging (fMRI) results.

Considering that acupuncture may have great relevance for modulation of sleep and mood through a potential central neural mechanism, in this trial fMRI—as a more intuitive and reliable detection technique—will be used to investigate the effectiveness and central neural mechanism in acupuncture treatment for perimenopausal insomnia by a comparison with western medicine. Furthermore, we will research the impact of acupuncture treatment for perimenopausal insomnia via changing the sleep architecture and neural function of the emotional neurocircuitry, consequently revealing the integrated effect mechanism of the emotional center function of acupuncture.

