### Hypothesis

According to the validity of acupuncture on perimenopausal syndrome, insomnia, and emotional disorder, as well as the influence of acupuncture on brain function, we hypothesize that acupuncture will improve the symptoms of perimenopausal insomniacs, and there will be a difference between acupuncture and medicine control based on the fMRI examination.

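### The imaging hypothesis is a difference between acupuncture and estazolam, but the only imaging group comparison the protocol specifies is a paired t test, which does not validly test that difference

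*Protocol article*

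**What the plan says.** All references are to the protocol article.

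- **Hypothesis:** "there will be a difference between acupuncture and medicine control based on the fMRI examination". The Background section frames the imaging aim the same way, as the "central neural mechanism in acupuncture treatment for perimenopausal insomnia by a comparison with western medicine".
- **fMRI examination procedure:** "Both of the intervention groups will be examined twice (before and after treatment"). Each patient therefore contributes two scans.
- **fMRI data processing:** "The cortex thickness, superficial area, and volumetric of every group will be compared using a paired" t test, with the threshold p "< 0.001, cluster size > 100 vertices". No other group comparison of imaging measures is named there. Two further steps follow. In the first, imaging changes and "clinical outcomes with significant statistical differences will be analyzed by multiple regression analysis". In the second, "Then we will acquire the brain regions correlated with an acupuncture clinical effect", using correlations between change in thickness or ReHo and clinical outcomes. Neither step names a treatment term.
- **Statistical analysis:** fMRI images are mentioned as something to be analyzed by differing approaches. One-way ANOVA, ANCOVA adjusting for baseline characteristics, and a nonparametric alternative are given for measurement data in general. None is linked to an imaging measure.

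**The concern.** The hypothesis is a contrast between two randomized arms, while the one test fixed for imaging group comparisons is paired. A paired test within an arm asks whether that arm changed. It does not ask whether it changed by a different amount from the other arm. Within-arm change also contains anything that moves both arms alike, such as the passage of time, repeat scanning or expectation, and it makes no use of the randomization.

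The imaging comparison is half of the formal hypothesis, and imaging is the stated reason for the study. If two within-arm maps were all that was available at the end, the natural temptation would be to report regions that changed under acupuncture but not under estazolam. That pattern is not a test of a difference, and it can appear often when the treatments have identical effects.

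**Working it through.** **Step 1. What can the paired test mean?**

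| Reading of the sentence | What it tests | Does it answer the hypothesis? |
|---|---|---|
| Before versus after, within each arm | Whether mean change in that arm is zero | No |
| Acupuncture versus estazolam | Nothing valid: patients are randomized 1:1 to independent groups and no matching is described | No |

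The first reading is the more natural one, because each arm is scanned twice and the sentence refers to every group. It remains an inference from loose wording. The conclusion is the same on both readings.

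**Step 2. Does anything else in that section fill the gap?** The regression and correlation steps relate brain change to clinical outcomes, which serves the separate objective of linking brain and clinical effects. ReHo appears only in those steps, so the one functional measure has no group test at all.

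**Step 3. How misleading could two within-arm tests be?** The plan gives no figure to reproduce here: the Sample size section states no effect size, SD or power. The inputs are:

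- n = 20 per arm (Sample size)
- p < 0.001 (fMRI data processing), taken as two-sided
- an assumed standardized change d, in units of the SD of change, identical in both arms

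The critical value is t(19 df) = 3.883. The power of one paired test is p = P(|T| > 3.883), where T is noncentral t with 19 df and noncentrality d√20. The arms are independent, so the probability that exactly one is significant is 2p(1 − p).

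| d (assumed) | d√20 | p | 2p(1 − p) |
|---|---|---|---|
| 0.2 | 0.894 | 0.006 | 1% |
| 0.3 | 1.342 | 0.017 | 3% |
| 0.4 | 1.789 | 0.041 | 8% |
| 0.5 | 2.236 | 0.087 | 16% |
| 0.7 | 3.130 | 0.277 | 40% |
| 0.8 | 3.578 | 0.416 | 49% |
| 0.9 | 4.025 | 0.566 | 49% |
| 1.0 | 4.472 | 0.707 | 41% |
| 1.2 | 5.367 | 0.903 | 18% |
| 1.4 | 6.261 | 0.980 | 4% |

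For d = 0.8: 2 × 0.416 × 0.584 = 0.486. The curve cannot exceed 50%, and it is small at both ends. The figures are per location and ignore the rule requiring clusters of more than 100 vertices.

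**Step 4. What would a between-arm test of change cost in precision?** With equal SDs of change, the standard error of a within-arm mean change is SD/√20 = 0.224 SD. For the difference in change it is SD√(2/20) = 0.316 SD, larger by a factor of √2. By the exact noncentral t with 20 per arm, 80% power at two-sided 0.001 needs a difference in change of about 1.41 SD, and power at 0.8 SD is 17%. At two-sided 0.05 the corresponding figures are 0.91 SD and 69%.

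**Step 5. Secondary check on acquisition.** The examination section says "The MRI protocol for this study consists of the following parameters: high-resolution three-dimensional T1 weighting brain volume (Bravo) sequence scanning" and lists no other sequence. The processing section applies slice-timing correction and temporal filtering and uses ReHo, all of which need a functional time series. The two sections do not match.

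**The case against.** The strongest reply is that the Statistical analysis section supplies a between-group test. It mentions fMRI images and names ANOVA and ANCOVA for measurement data, and thickness, area, volume and ReHo are measurement data. That stands in part. A reader might infer that the imaging hypothesis will never be tested, or that the paired test is the only group test in the trial. The document does not support either statement, because the general tests are not excluded for imaging. They are not assigned to it either, whereas the imaging section fixes its own test and threshold.

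A second reply is that a condensed article may leave second-level contrasts to an analysis plan that is not shown. Silence alone would indeed be no finding. Here, however, the article chose a test, and that test does not answer its own hypothesis.

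Third, a reader might infer that the headline imaging claim will rest on comparing significance between two maps. No section says so, and paired before/after maps are unobjectionable as description. The probabilities above therefore apply only if the maps were used that way. Quoting the 49% alone would also mislead: it is the peak of the curve, and the documents support no particular effect size.

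Fourth, PSQI is the primary outcome, and imaging is in neither the primary nor the secondary list. That limits the consequences but does not remove imaging from the hypothesis.

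On acquisition, the instructions to lie quietly with eyes closed and stay awake suggest that a resting-state scan is intended. Incomplete reporting is the likelier explanation, and a reader should not conclude that functional data will not be collected.

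**Conclusion.** The point holds in this form: the protocol specifies no valid between-arm test for its between-arm imaging hypothesis. The paired test named either addresses a different question or is invalid for independent arms, and ReHo has no group test. This follows from the text and depends on no effect size.

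The size of the risk is conditional. If within-arm significance were read as a treatment difference when both arms truly change equally, exactly one arm would be significant with probability between about 1% (0.2 SD) and 49% (0.8 to 0.9 SD), falling to 4% at 1.4 SD. This rests on 20 evaluable patients per arm, two-sided p < 0.001, equal assumed standardized change, independent arms, a single location and no cluster rule. The primary PSQI comparison is not affected. The mismatch between the listed structural sequence and the functional processing is a secondary reporting point.

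**What to change.** In the section on fMRI data processing, make the imaging test a between-arm contrast of change. Either regress the post-treatment value on arm with the patient's baseline value as covariate, or test the arm-by-time interaction. Apply it to thickness, area, volume and ReHo, and state the threshold for each. Label the paired within-arm maps as descriptive.

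In the section on the examination procedure, reconcile the list of sequences with the processing by stating the functional acquisition from which ReHo is computed.

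The cost is a change of wording and one further model contrast. The contrast needs no extra patients, visits or scans, and the trial is still recruiting, so it can be fixed before the data are analyzed. The real downside is the larger standard error shown above: fewer regions will be declared, and at p < 0.001 only large between-arm differences will be detected reliably with 20 per arm.
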